##### Treatment and other data

Baseline care provider data will be collected from clinicians delivering treatment in both arms of TIGA-CUB to provide details of the treating clinician’s job title, band, length of time working in CAMHS, professional qualifications and additional training in specific therapeutic techniques. The following data covering the period from randomisation up to 4 months post randomisation will be collected from the CAPTs/CAMHS team (or by the researcher or authorised individuals from the research team with appropriate access), and from the CAPT clinical supervisors:Care pathway details (type, sessions offered and attended, including sessions where participants did not attend (DNAs) or could not attend (CNAs), dates and duration of sessions, CAMHS practitioners involved, family members involved, and mutually agreed end date)Re-referrals to, or re-referrals within, CAMHSReferral to other services (including mental health, social, criminal, education, etc.)A checklist of expected adverse events (based on those listed in this protocol), with space to specify others not listedSupervision details (intervention arm only).

All participants who enter TIGA-CUB will be considered part of the intention-to-treat (ITT) population and efforts will be made to follow them up whenever appropriate.

### Process evaluation

The process evaluation aims to understand the functioning of the intervention and to inform the development of a confirmatory trial protocol by identifying:Acceptability of recruitment processes, and reasons for non-consent to trial participationReasons for treatment dropout or withdrawal from trial processes (i.e. from further data collection, researcher follow-up visits or telephone or postal questionnaire follow-up)Acceptability of data collection measures and timing of data collection (i.e. burden)Possible adverse reactions to taking part in the trialCAPT, primary carer (and, if possible, child) perspectives on aspects of the intervention considered to be effective, and perceptions of mechanisms of changeProcesses and challenges of implementing the intervention from the perspective of the CAPTs involved.

A questionnaire will be given to all eligible participants during recruitment. Quantitative data will be collected on primary carers’ characteristics, and on their views of recruitment. At the end of the individual participant’s involvement in the trial, a second brief questionnaire will be sent to gather their views on taking part, on the intervention or other treatment received, and on the trial (except those participants withdrawing from postal questionnaires). If applicable, data will be collected on reasons for treatment dropout and/or for withdrawing from the trial. Free-text responses will be used to allow participants to provide additional feedback about their experiences of taking part in the trial, in addition to the closed questions used in the survey.

Qualitative data on participants’ experiences of the trial will be collected via semi-structured interviews. Consent for interview will be obtained separately from overall trial consent. Feedback will be sought from the following groups:Decided against participation when trial presented to themAgreed to participate in the trial and randomisedDeclined allocated treatment; dropped out of treatment and/or withdrew from the trial (but not the process evaluation).

In-depth, semi-structured qualitative interviews will be conducted (to data saturation – expected to be about 15 primary carers). Purposive sampling will be used to ensure a wide range of primary carer views, including where possible treatment completers, treatment dropouts, and those declining trial participation. For maximum variation, we will sample on child’s age and gender, and degree of CBCL change, where possible. We will also seek to recruit across centres to identify any centre-level differences. Interviews will seek to maximise understanding of the experiences of those taking part in the trial and, where applicable, their views of the intervention. Depending on age and willingness to participate, attempts will be made to gain some feedback from children (what they liked or did not like), with their primary carer present.

A topic guide will be used to guide the interview discussion and will ask about why participants took part (or not), the recruitment and randomisation process, their experiences of participation, concerns about participation, and burden of involvement. Interviews are expected to last 45 to 60 min. Interviews will be undertaken by a researcher with specific training and/or experience in conducting in-depth, exploratory interviews.

The timing of contact will vary between participant groups:Those recruited within the first 3 months of the recruitment period will be contacted after the end of treatment and consent will be sought for interview approximately 8 months after randomisation, to capture longer-term views of the treatment and to assess the burden of data completion on participantsThose recruited within the last 4 months of the trial will be contacted after, and interviewed within, 2 months of end of therapy to capture the experiences of treatment and recruitmentThose who decline trial involvement will be contacted within a month of declining the trial.

All CAPTs taking part in the trial will be invited to take part in a focus group discussion to talk about their experiences of using mPCP. The focus group will take place at the end of the trial once all dyads have completed mPCP. A topic guide will be used to explore views about trial design, factors enabling or inhibiting successful recruitment, intervention delivery, and data collection. Participants will also be asked how mPCP fits with their usual clinical practice, aspects of mPCP considered effective/perceived mechanisms of change, and unanticipated or adverse impacts on services or dyads.

### Health economics

This component is included to check the completeness and ability to obtain resource-use data from dyads about both NHS and private costs and quality of life. Wherever possible, unit costs for resources will be obtained from national sources such as the *British National Formulary* (BNF) [63] and the Personal Social Services Research Unit (PSSRU) Costs of Health and Social Care [64]. NHS and Social Service resource use will be identified through direct observation of the treatment provided within the feasibility trial and through the structured questionnaire for collection of data on all other service use. We will assess the level of completeness of EQ-5D-Y as reported by the child and by the primary carer and evaluate any discrepancies using Quality-adjusted Life Years (QALYs) as the outcome.

### Outcomes

Outcomes relate to feasibility of recruitment, therapeutic delivery, retention in treatment, and outcome data collection:

Recruitment methods, uptake, and follow-up: (1) number of dyads screened for eligibility, (2) proportion of carers from eligible dyads consenting to the trial, (3) proportion of consenting dyads randomised, (4) reasons for non-participation, and (5) proportion of randomised dyads completing the trial, number of withdrawals from follow-up data collection, reasons for withdrawal, number of losses to follow-up.

Therapeutic delivery: (1) proportion of dyads randomised to the intervention arm, proportion randomised to, and seen by, the allocated CAPT; proportion of dyads successfully completing the required number of mPCP sessions specified in the manual; number of those dyads where there was a mutually agreed earlier termination, including reasons for early termination; early (non-agreed) dropouts from the intervention, including reasons for early dropout; (2) methods developed for measuring dyad treatment attendance and CAPT adherence to the manual, including the number of mPCP sessions offered, attended, and missed, and evidence of the appropriate use of the clinical approach advocated in the intervention manual; (3) preliminary assessment of the acceptability of the intervention, including negative outcomes, serious adverse events (SAEs), and related and unexpected SAEs (RUSAEs) (all RUSAEs occurring from the date of consent up to 4 (8, where applicable) months post randomisation will be recorded, reviewed by the chief investigator, and reported to the Research Ethics Committee (REC) and the sponsor within 15 days; (4) mapping of the range of standard care (CAMHS/external) pathways across arms; and (5) number of patients where the standard care pathway is known.

Follow-up data collection: (1) proportion of dyads with self-reported outcome data, proportion obtained at 4 months (and 8 months if applicable); (2) proportion of dyads with teacher-reported outcome data obtained at baseline and 4 months; (3) proportion of dyads with self-reported health economic data at 4 months; (4) proportion of dyads for whom it was possible to collect routine data, if this is pursued; (5) missing-item-level data on self-reported questionnaires; and (6) number of unblinding events of trial researchers over the data collection periods.

Statistical outcomes: (1) variability of self-reported outcome measures at baseline, 4 months; (2) clustering effect (ICC – intracluster correlation coefficient) relating to CAPTs in the intervention arm; (3) difference in self-reported outcomes available at 4 months per treatment arm; and (4) 95% confidence intervals (CI) for differences in outcomes between arms.

Health economic outcomes: (1) variability of the self-reported and proxy-reported EQ-5D-Y at baseline and 4 months; (2) completeness of and ability to obtain resource use data from dyads about both NHS and private costs; (3) exploratory cost-effectiveness analysis; and (4) suitability of a decision analysis model and appropriate time horizon to assess cost-effectiveness in the confirmatory RCT.

Process evaluation outcomes: (1) understanding of the recruitment process (with ideas for improving recruitment); (2) views on the intervention/trial; (3) reasons for declining to take part, dropping out of treatment, or withdrawing from the trial; (4) understanding of the contextual factors affecting involvement in the trial; (5) understanding of the barriers to, and enablers for, implementation; and (6) understanding of possible mechanisms of change.

Qualitative: establishment of (1) processes for successful recruitment of CAPTs; (2) procedure for training of CAPTs; (3) method for agreeing CAPT competence; and (4) procedure for ongoing supervision of CAPTs.

### Monitoring treatment attendance and adherence

Data will be collected on child and primary carer attendance at sessions. The steps taken to ensure consistency in the use of the mPCP intervention will also be recorded (attendance at training and supervision sessions for CAPTs, adherence of CAPTs to the manual). Child and primary carer mPCP intervention sessions will be tape-recorded where consent for this has been obtained from the primary carer, with the assent of the child. CAPT supervision sessions will also be tape-recorded, with consent. The chief investigator will review a selection of the mPCP tape-recorded intervention and supervision sessions to ensure, and allow reporting of, overall adherence of CAPTs to the manual. We will develop a coding and scoring system for assessing CAPT adherence to the manual, with a global rating of overall adherence.

### Sample size

The trial is designed to determine the feasibility of a confirmatory trial, not to assess proof of concept or evaluate effectiveness. It is generally recommended for feasibility studies that the analysis data set comprises a minimum of 30 participants per arm [65–67]. However, based on a review of the academic literature [68–78], estimates of the standard deviation (SD) of CBCL total score are already available, indicating that it is reasonable to assume a common SD across arms. We therefore require a minimum of 30 evaluable dyads across the arms to confirm the SD. Loss to follow-up has ranged from 8 to 38%, so we need up to 50 dyads randomised to guarantee 30 evaluable dyads. Treatment attendance has ranged from 40 to 95%. Assuming that we can reduce loss to follow-up to 10% at 4 months, randomising 60 dyads on a 1:1 basis will allow us to estimate the pooled SD with a 95% CI with expected width of 0.39 multiplied by SD, loss to follow-up with a 95% CI with expected width ± 7%, and treatment attendance in the intervention arm with a 95% CI with expected width of between ± 8 to 18%. It is expected that 60 dyads will provide sufficient opportunity to establish robust recruitment and retention strategies for a confirmatory trial.

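### Minor: with 60 dyads and 10% loss the follow-up interval is ±8%, not ±7%, and 50 dyads do not guarantee 30 evaluable

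*Protocol article*

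**What the plan says.** All the relevant statements are in the Sample size section of the protocol article.

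- Minimum needed: "We therefore require a minimum of 30 evaluable dyads across the arms to confirm the SD".
- Inflation for loss: "Loss to follow-up has ranged from 8 to 38%, so we need up to 50 dyads randomised to guarantee 30 evaluable dyads".
- Planning assumption: "Assuming that we can reduce loss to follow-up to 10% at 4 months".
- Planned number: "randomising 60 dyads on a 1:1 basis".
- Precision claimed for loss: "loss to follow-up with a 95% CI with expected width ± 7" per cent.
- Attendance: "Treatment attendance has ranged from 40 to 95" per cent, with precision given as "treatment attendance in the intervention arm with a 95% CI with expected width of between ± 8 to 18" per cent.

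The same sentence gives the expected width of the 95% interval for the pooled SD as 0.39 × SD.

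**The concern.** The number of dyads, the assumed loss rate and the confidence level are all stated, so the loss precision can be recomputed directly. It does not come out at the printed value, although its neighbours in the sentence do. The word *guarantee* also attaches certainty to a calculation that only balances on average.

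The stakes are modest. These figures are part of the quantitative support for randomising 60 dyads. The Statistical analysis section says that follow-up in this trial will inform the loss rate used to size the confirmatory trial. A reader should therefore be able to rely on the stated precision, and on what a given number of dyads secures at the worst loss cited.

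**Working it through.** **Inputs (all from the Sample size section).** 60 dyads randomised 1:1, so 30 in the intervention arm; assumed loss 10%; past loss 8% to 38%; past attendance 40% to 95%; minimum 30 evaluable across arms; 95% confidence.

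**Step 1. Reproduce the figures that agree, to identify the formula.** Half-width h = 1.96 × √(p(1−p)/n).

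- Attendance 95%, n = 30: 1.96 × √(0.95 × 0.05/30) = 7.8%, printed as 8.
- Attendance 40%, n = 30: 1.96 × √(0.40 × 0.60/30) = 17.5%, printed as 18. (The widest point in the range, 50% attendance, gives 17.9%, also 18.)
- Pooled SD with 54 evaluable dyads (90% of 60), chi-square interval on 53 degrees of freedom: width 0.394 × SD, printed as 0.39.

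So the attendance figures are this formula rounded to the nearest whole per cent.

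**Step 2. Apply the same formula to loss to follow-up.** p = 0.10, n = 60:

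1.96 × √(0.10 × 0.90/60) = 7.59%, which rounds to 8. The article prints 7.

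Other interval methods at 6 losses out of 60 do not bring it down to 7: the Wilson half-width is 7.7%, Jeffreys 7.6%, Agresti–Coull 8.1% and Clopper–Pearson 8.4%.

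**Step 3. What would give ±7%.**

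- At 10% loss: n = 1.96² × 0.09/0.07² = 70.6, so 71 dyads.
- With 60 dyads: loss near 8%, where 1.96 × √(0.08 × 0.92/60) = 6.9%.

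For context, at 38% loss with 60 dyads the half-width is 1.96 × √(0.38 × 0.62/60) = 12.3%.

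**Step 4. The 50 dyads.** Inflating for expected loss: 30/(1 − 0.38) = 48.4, so 49; and 50 × 0.62 = 31 evaluable on average. As an expected-value calculation, 50 is correct.

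As a guarantee it fails. Let X be the number evaluable, binomial with each dyad retained independently:

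| Randomised | Loss | P(X ≥ 30) |
|---|---|---|
| 50 | 30% | 0.95 |
| 50 | 38% | 0.67 |
| 58 | 38% | 0.96 |
| 60 | 38% | 0.98 |

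At 38% loss, 50 dyads fall short of 30 about one time in three. The probability first exceeds 0.95 at 58 dyads, and the planned 60 are above that.

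**The case against.** **A different method could explain ±7%.** The article speaks of an expected width. Averaging the half-width over the binomial distribution of losses (n = 60, p = 0.10) gives 7.4%, which rounds to 7. But the same averaging gives 6.6% at 95% attendance, which would print as 7 and not 8, and 17.2% at 40% attendance. The lower attendance figure rules it out as the one method behind the sentence. Truncating 7.59 remains possible, so the cause of the slip is not known; only the mismatch is. A reader might infer that the figure was taken at 8% loss, the most favourable value cited. The arithmetic fits, but the article states 10% and nothing in it shows that 8% was used.

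**The slip is immaterial.** This largely stands. The gap is 0.6 percentage points, and the confirmatory trial will draw on the observed rate with its own interval, not on this planning figure. A reader might infer that the precision of the trial is seriously overstated or that 60 is too few. The figures do not support either.

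**The 50 is an intermediate step.** This also stands. The inflation is right on expected numbers, and the trial randomises 60. What does not stand is the claim of certainty.

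**Precision is shown at one loss rate only.** A reader might infer selective presentation, because attendance precision spans its whole range. The 10% is openly given as an assumption and the 8% to 38% range is printed in the same paragraph, so this is no error. Nor is the choice of interval method for reporting proportions, which belongs to the analysis plan.

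**Conclusion.** The point holds as a minor correction. Two statements in the Sample size section are wrong as written: the loss precision should be ±8% (7.6%) at the stated 60 dyads and 10% loss, and 50 dyads give about a 67% chance, not a certainty, of 30 evaluable at 38% loss. The first conclusion rests on the attendance figures having been rounded to the nearest whole number by the formula in Step 1. The second rests on independent losses at a common rate; correlated losses, for example within site, would change the exact probability but could not turn it into a guarantee. Neither point calls for a larger trial: 60 dyads give about a 98% chance of reaching the minimum even at the worst loss cited, and no feasibility conclusion is affected.

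**What to change.** In the Sample size section:

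1. Give the loss precision as ±8% (or ±7.6%) at 10% loss. Optionally add that it would be about ±12% if loss reached 38%.
2. Replace *guarantee* with *expect* for the 50 dyads, or state instead that 60 dyads give about a 98% chance of at least 30 evaluable at 38% loss. The second wording is the more useful, because it supplies a reason for choosing 60 that the article does not currently state.

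The cost is two phrases of text. The number randomised, the conduct of the trial and the analysis stay as they are.

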### Statistical analysis

The trial statisticians will be responsible for statistical analysis. The analysis plan outlined in this section will be reviewed and a final, more detailed statistical analysis plan will be written before any analysis is undertaken. Any changes to the finalised analysis plan and reasons for change will be documented. There are no planned subgroup analyses. No formal analyses are planned until after the trial is closed to recruitment and all patients have been randomised. Final analysis will be carried out when all available outcome data have been received.

The recruitment strategy will be evaluated by summarising the screening, eligibility, consent, and randomisation stages, clearly separating the child from their primary carer, including numbers of dyads involved during each stage. Reasons for non-participation in the trial will be summarised, dyad retention during follow-up, including number of dyads completing/withdrawing from the trial and reasons for withdrawal, will be presented overall and by treatment arm.

Receipt of mPCP will be evaluated by summarising the proportion of dyads attending at least one session and those successfully completing the required amount of mPCP as specified in the manual (or fewer, as determined by the CAPT), both individually and as a dyad. The number of sessions and pattern of attendance will also be summarised. The number of early mutually agreed terminations and non-agreed dropouts from the intervention arm will be reported and the reasons for dropout summarised, where available. The method for measuring mPCP treatment attendance by the dyad will be agreed and summarised, i.e. number of sessions attended and length of sessions attended by child and primary carer, respectively, and a method for measuring manual adherence will be developed, including CAPT attendance at mPCP training, regular attendance and presentation at clinical supervision, development of an appropriate scoring system designed to assess manifestation by CAPTs of key components of the manual, review of a randomly selected subset of tape-recorded child and primary carer mPCP sessions and CAPT supervision sessions, employing this scoring system. The range of co-interventions and TaU (in CAMHS) in both arms will be summarised by treatment arm, as will referrals outside of CAMHS. The feasibility of obtaining information on care provided outside of the trial treatments will be assessed by the number of dyads for which this care is known, overall and by treatment arm.

The feasibility of obtaining the confirmatory trial’s primary and secondary outcome data will be assessed by summarising the proportion of dyads with available self-reported outcome data by method of obtainment, overall and by treatment arm. Levels of, and where possible predictors of, missing self-reported outcome data, both at the individual-item level and for entire outcome measures, will be reported overall and by treatment arm.

In order to inform the sample size/power calculation for the confirmatory trial, we will assess the variability (SD) of the CBCL total score in the intervention and control arms to confirm the SD to be used. The clinically relevant difference will be assessed by establishing the mean scores (and corresponding 95% CIs) of the CBCL total score in the control arm and by seeking clinical opinion. Point and interval estimates of the eligibility, recruitment, and treatment attendance rates in this feasibility trial, along with the number of participants successfully followed up, will also help to inform the sample size by allowing estimation of the likely loss to follow-up rates that will occur, and will allow assessment of the feasibility of recruitment for the confirmatory trial. An investigation of the clustering effect (ICC) relating to the CAPTs will be carried out to aid sample size calculation. The difference in outcomes between the control and intervention arms at each point will be reported, with 95% CIs constructed around these differences. No formal testing will be done on this data.

### Health economic analysis

The health economist will be responsible for health economic analysis. We will evaluate the completeness of data and rate of missing data on individual questions to inform the methodology and the perspective to be used within the confirmatory trial. Although the cost-effectiveness analysis at this stage will only be exploratory, the incremental cost-effectiveness of a second-line mPCP intervention compared to TaU for children aged 5–11 years with treatment-resistant CD and their primary carers will be examined. We will also calculate indicative costs for the interventions.

Utility weights will be obtained from the EQ-5D-Y data as reported by the child or by the primary carer as a proxy-respondent for the child and collected as part of the feasibility trial follow-up. We will also consider aggregating utility gains, accumulating child and primary carer utility obtained from the EQ-5D. An exploratory cost-effectiveness analysis will be carried out on complete cases only (i.e. completion at all time points) and with imputations (multiple imputations based on age, gender, and treatment), and a set of within-feasibility trial sensitivity analyses will be undertaken.

